#### Waiting list control (WLC)

Participants of the WLC will not get any kind of active training intervention. But they are informed that monitoring and reflecting on their drinking behavior by completing online-assessments can be a first step toward healthier drinking habits. In addition, participants will get access to the training after the 6-month follow-up assessment.

### Measures

#### Primary outcome

Primary outcome will be the self-reported alcohol consumption (standard units) during the 7 days prior to T2, using the Timeline Followback (TLFB) method [52]. The TLFB has been shown to be a valid and reliable procedure to document recent drinking histories [53]. The procedure has been proven to capture drinking levels very well compared to a daily diary [54]. It has been also validated as a web-based version [55]. Respondents retrospectively record their daily drinking by choosing the amount and kind of drinks they had out of a set of typical alcoholic drinks (e.g. a 330 ml bottle of beer or a 100 ml glass of wine). These quantities will be automatically converted to alcohol standard units and added to calculate the total sum score of units for the last 7 days.

As a secondary drinking measure, participants will be coded as responders if their drinking remains within the margin of low-risk, i.e., drinking not more than 14 (women) or 21 (men) standard units per week. Besides the drinking level, several other variables will be assessed as secondary outcomes (Table 2).

**Table 2 Tab2:** Secondary outcome measures and assessment points

Outcome measures	T1	T2	T3
Alcoholic Drinks (Timeline Followback method)	✓	✓	✓
Alcohol Problems Questionnaire (APQ)	✓		✓
Readiness to Change Questionnaire (RTCQ)	✓	✓	✓
Depression Anxiety Stress Scale (DASS-21)	✓	✓	✓
Irritation Scale (IS)	✓	✓	✓
Effort Reward Imbalance Questionnaire (ERI-SF)	✓		✓
Work Limitations Questionnaire (WLQ)	✓	✓	✓
Single-Item Presenteeism Question	✓	✓	✓
Single item question on work ability	✓	✓	✓
General Self-Efficacy Scale (GSE)	✓	✓	✓
Assessment of Quality of Life (AQoL-8D)	✓	✓	✓
Trimbos and institute of Medical Technology Assessment Cost Questionnaire for Psychiatry (TiC–P-G)	✓		✓
Attitudes toward seeking psychological help (ATSPPH-SF)	✓	✓	✓
Use of other health services		✓	✓
Negative-Effects of Psychotherapy Inventory (INEP)			✓
Client Satisfaction Questionnaire (CSQ-8)		✓	

T1 = baseline assessment before randomization, T2 = post assessment after 6 weeks, T3 = follow-up assessment after 6 months

#### Secondary outcome measures

##### Alcohol-related problems

The Alcohol Problems Questionnaire (APQ) [56] will be used to measure common (23 items, e.g. “Have your friends criticized you for drinking too much?”) and occupational (8 items, e.g. „Have you been unable to arrive on time for work due to your drinking?“) alcohol-related problems. All items apply to a 6-month period prior to the assessment and can be answered by 1 = “Yes” or 0 = “No.”. Item scores can be added to calculate a common problems subdomain score (APQC) ranging from 0 to 23 and a work problems subdomain score (WORK), ranging from 0 to 8. The subdomains show internal consistencies of α = .92 for the APQC and α = .82 for WORK [57].

##### Readiness to change

The Readiness to Change Questionnaire (RTCQ) [58, 59] is based on the stage of change model of Prochaska and DiClemente. It consists of three subdomains with four items each, corresponding to the stages through which a person moves in an attempt to resolve a drinking problem: precontemplation (e.g. “I don’t think I drink too much”), contemplation (e.g. “I enjoy my drinking, but sometimes I drink too much”), and action (e.g. “I am trying to drink less than I used to”). Respondents rate all items on a five-point Likert-type scale, ranging from 1 = “strongly disagree” to 5 = “strongly agree”. The subdomains show internal consistencies of α = .82 for precontemplation, α = .86 for contemplation, and α = .78 for action.

##### Depression, anxiety, and stress

The Depression Anxiety Stress Scale (DASS-21) [60] will be used to assess symptoms of depression, anxiety, and stress with seven items each. Respondents rate each item (e.g. “I found it hard to wind down”) on a four-point Likert-type scale, ranging from 0 = “Did not apply to me at all” to 3 = “Applied to me very much, or most of the time”. Total scores of the three subdomains range from 0 to 21. The DASS-21 shows internal consistencies of α = .88 for depression, α = .82 for anxiety, and α = .90 for stress [61].

##### Work-related stress

We will use two different measures to assess work-related stress. The Irritation Scale (IS) [62] operationalizes work-related stress in terms of cognitive (CI) and emotional irritation (EI), as reactions on uncertainty in the working environment. The CI subdomain consists of three items (e.g. “Even at home I often think of my problems at work.”). The EI subdomain consists of five items (e.g. “I get grumpy when others approach me.”). Respondents rate all items on a seven-point Likert-type scale (1 = “strongly disagree”, 2 = “largely disagree”, 3 = “rather disagree”, 4 = “moderately agree”, 5 = “partly agree”, 6 = “largely agree”, 7 = “strongly agree”). The items are added to a total irritation scale. Both subdomains show good internal consistencies, ranging from α = .85 to .97 [62].

The Effort Reward Imbalance Questionnaire – Short Form (ERI-SF) [63] assesses stress based on the model of effort-reward imbalance. The subdomain “effort” consists of three items (e.g. “I have constant time pressure due to a heavy work load”). The subdomain “reward” consists of seven items (e.g. “My job promotion prospects are poor”). Respondents rate all items on a four-point Likert-type scale (1 =”strongly agree”, 2 =”agree”, 3 =”disagree”, 4 =”strongly disagree”). The subdomains show moderate to good consistencies, α = .77 for effort and α = .82 for reward [64].

##### Presenteeism

We will use the short form of the Work Limitations Questionnaire (WLQ-8) [65, 66]. It consists of eight items, measuring the degree to which health problems interfere with the ability to perform in the job. All items are to be rated on a five-point Likert-type scale, ranging from 1 =”the whole time” to 5 = “none of the time” (e.g. “In the past 2 weeks, how much of the time did your physical health or emotional problems make it difficult for you to concentrate on your work?”). In addition, we will use an adapted version of the Single-Item Presenteeism Question (“To what extent has your physical or mental health problems affected your performance at work over the past 30 days?”) [67], ranging from 0 = “not at all” to 10 “extremely”, and a single item question on work ability (“Current work ability compared with the lifetime best”) [68], ranging from 0 = “completely unable to work” to 10 “work ability at its best”.

##### Self-efficacy

The 10-item General Self-Efficacy Scale (GSE) [69] assesses a general sense of perceived self-efficacy, with the goal of predicting the ability to cope with daily problems and adapt after experiencing stressful life events. The respondents evaluate statements on a four-point Likert-type scale, ranging from 1 = „not at all true” to 4 = “completely true” (e.g. “I can typically handle whatever comes my way”). A higher score indicates higher self-efficacy. The item values can be added to a total score, ranging from 10 to 40. The internal consistency of the GSE is varying from α = .76 to .90 in different samples [69].

##### Attitudes toward seeking professional psychological help

The Attitudes Toward Seeking Professional Psychological Help Scale – Short Version (ATSPPHS-SF) [70] assesses attitudes toward seeking professional help for psychological problems. Respondents rate all of the ten items of this scale on a four-point Likert-type scale, ranging from 0 = “disagree” to 3 = “agree” (e.g. “If I believed I was having a mental breakdown, my first inclination would be to get professional attention.”). The items can be added to a total score, ranging from 0 to 30. The scale shows an internal consistency of α = .84.

##### Negative side-effects

Adverse effects will be measured with an adapted version of the Negative-Effects of Psychotherapy Inventory (INEP) [71]. The version used in this study consists of 15 items, assessing negative effects participants experienced within or after the completion of the web-based training. The INEP covers the following domains: negative intrapersonal changes, negative effects in an intimate relationship, family/friends, perceived dependence on the eCoach/intervention, and stigmatization (e.g. “I am anxious that my colleagues or friends could find out about my training participation”). Respondents rate all items on a four-point Likert scale, ranging from 0 = “no agreement at all” to 3 = “total agreement”. For each item, participants also state whether they attribute the adverse effects on the training participation or on other factors. Only item scores of those negative effects that were attributed on participating in the training are added to the total score. Higher total scores indicate more negative effects. The INEP shows an internal consistency of α = 0.85.

##### Course evaluation

To evaluate the course satisfaction we used the Client Satisfaction Questionnaire (CSQ-8) [72, 73] and adapted it to the context of web-based trainings. The CSQ consists of eight items, measuring the global client’s satisfaction with the training. Respondents rate all items (e.g. “How would you rate the quality of service you received?”) on a four-point Likert-type scale, with different responses (e.g. 1 = “Poor” to “Excellent”). Previous research indicated a high internal consistency of α = .92 for the general version [74] and α = .92 for the adapted version [75, 76].

##### Quality of life

The Assessment of Quality of Life (AQoL-8D) [77] will be used as multi-attribute utility instrument. This measure consists of 35 items, covering eight subdomains of health-related quality of life which can be combined to a physical super dimension (independent living, pain, senses) and a mental super dimension (mental health, happiness, coping, relationships, self-worth). The respondents rate all items on a four-, five-, or six-point Likert-type scale, ranging from 1 = “very rarely” to 4 = “most of the time” (e.g. “Thinking about how often you experience serious pain: I experience it…”), from 1 = “never” to 5 = “always” (e.g. “How often do you feel socially excluded or left out?”), or from 1 = “very satisfying” to 6 = “very unpleasant” (e.g. “Your close relationships (family and friends) are:”). The scale shows internal consistencies of α = .88 for the physical health dimension and α = .96 for the mental health dimension [77].

##### Cost measure

A German version of the Trimbos and Institute of Medical Technology Assessment Cost Questionnaire for Psychiatry (TiC–P-G) [78] will be used to record direct and indirect medical costs over the previous three months. Direct costs can be derived from information on the participants’ use of health services (e.g. general practice visits, sessions with psychiatrists, hospital days). To assess indirect costs participants register the number of “work loss” days (absenteeism from work) and the number of “work cut-back” days, i.e., days on that they were showing up for work despite of feeling ill (presenteeism). The questionnaire shows a good retest-reliability and achieves comparable results between patient-reported data and data derived from medical registrations [78].

### Sample size calculation

We expect that both intervention groups will be, compared to the control group, superior in terms of the primary outcome from T1 to T2. The latest meta-analysis on mainly unguided web-based interventions for reducing alcohol consumption [28] yielded an overall effect size of d = 0.20. Subgroup analyses revealed no significant differences in effect size regarding the type of intervention (personalized normative feedback vs. more extended interventions) or the number of sessions. However, in an earlier meta-analysis, the same research group found indications for extended interventions to be more effective than personalized normative feedback with an average effect size of g = 0.61 for extended and g = 0.27 for PNF [79]. Because GET.ON CWT contains evidence-based cognitive-behavioral components over and above PNF and motivational interviewing, we expect a slightly greater effect than the one that was found in the meta-analysis [28]. We aim to include 528 participants. This sample size will allow us to detect an effect size of d = 0.30 based on a power (1-ß) of 80 % and an alpha error of .05 in a two-sided test, calculated using G*Power software [80].

### Statistical analyses

The trial will be conducted in compliance with the study protocol and the Declaration of Helsinki. Aiming at an intention-to-treat design, we will include all participants who will have been randomly assigned to the conditions. Missing data will be handled using multiple imputations. In addition, per protocol analyses (PPA) will be performed, including only participants followed the intervention outlined in the study protocol. The evaluation will be conducted in accordance with the consolidated standards of reporting trials (CONSORT) [81].

### Clinical evaluation

Analyses of covariance with baseline scores as covariate will be conducted to explore the effects of the interventions compared to the control group on all primary and secondary outcomes. A-priori contrasts will be defined to test the separate effects of the guided and unguided interventions compared to the control condition. For all analyses, Cohen’s d will be calculated by subtracting the average change scores from baseline to post-assessment (T1-T2) of one study group from the other one and then dividing it by the pooled standard deviations of the change scores. We will also calculate the number needed to treat (NNT) with adherence-focused guided and unguided CWT to achieve one response, i.e., complying with the low-risk guideline, compared to the control group. For all statistical analyses, significance level will be set at p < .05 for two-sided tests.

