### Participants & procedure

#### Inclusion and exclusion criteria

We include (a) working people, (b) who are above the age of 18, (c) who report drinking of at least 14/21 (women/men) standard units per week, (d) who have a score of at least 6/8 for women/men on the Alcohol Use Disorders Identification Test (AUDIT) [36], (e) who have Internet access, (f) who have sufficient German language reading and writing skills (self-reported), and (g) who are willing to give informed consent. We exclude subjects (a) who indicate that they have been diagnosed with psychosis or a drug dependency in the past, (b) who show a notable suicidal risk as indicated by a score greater than 1 on BDI [37] Item 9 (“I feel I would be better off dead”), (c) who have received medication or have begun psychotherapy to treat their problematic alcohol consumption, and (d) who are participating in another study on online-health training of our study group at the same time.

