#### Assessment of eligibility and randomization

The trial will be open to all people who meet criteria listed above. After registering, applicants receive an email with detailed information about the study procedures. Then, they will be informed that they can withdraw from the intervention and/or study at any time without any negative consequences. Applicants who continue to participate in the study will be asked to complete an online screening questionnaire. They must fulfill all criteria of inclusion and none of the exclusion criteria, have to complete the baseline assessment (T1), and return the informed consent form to participate in the study.

Eligible applicants will be randomly allocated in a 1/1/1 ratio to one of the three trial arms: adherence-focused guided CWT, unguided CWT, or WLC. Randomization will take place at an individual level. The allocation will be performed by an independent researcher not otherwise involved in the study, using an automated computer-based random integer generator (randomisation.eu). During the randomization process, allocation will be concealed from participants, researchers involved in recruitment, and eCoaches. After being informed about the outcome of the randomization, participants in the two intervention groups will receive immediate access to the training. All data is collected using a secure web-based assessment system (AES, 256-bit encrypted).

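### The primary ANCOVA names only the baseline score as covariate; adding sex, which is known for every participant, may recover a little precision at almost no cost

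*Protocol article*

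**What the plan says.** - **Model.** Methods, Clinical evaluation: "Analyses of covariance with baseline scores as covariate will be conducted to explore the effects of the interventions compared to the control group". This covers all primary and secondary outcomes, and no further covariate is named. The tests of interest are pairwise: "A-priori contrasts will be defined to test the separate effects of the guided and unguided interventions compared to the control condition".
- **Outcome.** Methods, Primary outcome: "Primary outcome will be the self-reported alcohol consumption (standard units) during the 7 days prior to T2". It is a continuous total with no sex-specific threshold.
- **Sex.** Inclusion and exclusion criteria: entry is for people "who report drinking of at least 14/21 (women/men) standard units per week", with AUDIT cut-offs that also differ by sex. Eligibility cannot be decided without knowing sex, so it is available for everyone randomised.
- **Size.** Sample size calculation: 528 participants, d = 0.30, 80% power, two-sided 5%. No credit is taken there for any covariate.

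**The concern.** A baseline-adjusted ANCOVA removes the part of a sex difference that runs through the measured T1 total. It would remove all of it if that total were an exact measure of usual drinking and sex had no other influence. A total for one week is not exact. If men usually drink more than women, a man and a woman with the same T1 total tend to move back towards different usual levels by T2. Sex then predicts T2 units at equal T1 units, and a model without sex leaves that variation in the residual.

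At stake is efficiency only: the standard error of the two primary contrasts could be somewhat larger than the collected data require.

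**Working it through.** **1. The stated sample size.** A two-sample t-test for one pairwise contrast with d = 0.30, two-sided alpha 0.05 and 80% power needs 176 per arm. 3 × 176 = 528, with power 80.1%. The plan's figure reproduces exactly as an unadjusted comparison and does not depend on the covariates.

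**2. Mechanism.** Let usual drinking have mean μ_M in men and μ_F in women, and let λ be the slope of T2 on T1 within each sex. Setting aside treatment effects and general change, the expected T2 total is λ·T1 + (1 − λ)·μ_sex. The sex gap at equal T1 is therefore (1 − λ)(μ_M − μ_F). It is zero if the usual levels are equal or if T1 is free of noise (λ = 1). For example, λ = 0.5 and a gap of 7 units in usual drinking leave 0.5 × 7 = 3.5 units at equal T1.

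**3. From that gap to residual variance.** The documents give no distribution, so these inputs are assumed: half men; T1 equal to the cut-off (21 or 14) plus a gamma variable with shape 1.2 and scale 12; slope 0.5; residual SD 10 to 20.
- Variance of T1 within sex: 1.2 × 12² = 172.8. Between sexes: 0.25 × 7² = 12.25.
- Variance of the sex indicator given T1: 0.25 × (1 − 12.25/185.05) = 0.233.
- Share of residual variance removed by sex = 0.233·gap² / (0.233·gap² + SD²).

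| Gap at equal T1 | SD 10 | SD 20 |
|---|---|---|
| 0 units | 0% | 0% |
| 3.5 units | 2.9/102.9 = 2.8% | 2.9/402.9 = 0.7% |
| 7 units | 11.4/111.4 = 10% | 11.4/411.4 = 2.8% |

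**4. Simulation of entrants.** This assumed log-normal usual drinking, noisy 7-day totals, 14/21 entry and half men among applicants. The log-SD of usual drinking was 0.3 to 0.7 and that of the weekly noise 0.2 to 0.5.
- Medians of 30–35 (men) and 20–24 (women): sex removed 0.1% to 8.8% of the residual variance left after T1. With log-SD 0.7 for usual drinking the range was 0.1% to 1.8%; with 0.5 it was 0.4% to 3.7%. Values near 8% appeared only with the widest gap (35 against 20) and the narrowest spread.
- Medians of 26 and 24: 0.0% to 0.4%.
- Equal medians: 0% to about 0.5%.

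A working range is therefore about 0% to 9%. The 10% corner in step 3 lies just above it and needs both the largest gap and the smallest residual SD.

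**5. Power.** Let r be the correlation of T1 with T2 and ρ the partial correlation of sex with T2 given T1, both assumed. In the normal approximation, power = Φ(0.30·√(176/2)/s − 1.96), with s = √(1 − r²)·√(1 − ρ²) and 0.30·√88 = 2.814.

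| ρ (ρ²) | SE multiplier √(1 − ρ²) | Power, r = 0.3 | Power, r = 0.5 |
|---|---|---|---|
| 0 (0%) | 1.000 | 83.9% | 90.1% |
| 0.10 (1%) | 0.995 | 84.3% | 90.4% |
| 0.20 (4%) | 0.980 | 85.3% | 91.3% |
| 0.30 (9%) | 0.954 | 87.1% | 92.6% |

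The first row is the planned model before dropout. Sex adds 0.3 to 0.4 points at ρ = 0.10 and 2.5 to 3.2 points at ρ = 0.30. In participants, 9% is worth 528/0.91 − 528 ≈ 52 and 1% about 5.

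**The case against.** The strongest reply is that nothing here is an error. Baseline-adjusted ANCOVA in a randomised trial is valid, takes in the main prognostic variable, and already lifts power above the planned 80%. Only a condensed article is shown, and further covariates may be in a full protocol or analysis plan. No figure in the documents shows that sex matters once T1 is in the model. The entry cut-offs do not show it: with equal usual drinking they leave sex explaining almost nothing. All of this stands, and it limits the point to an optional gain of uncertain size. It does not remove the point, because the article states the covariate outright and the change is nearly free even if sex turns out to add nothing.

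Four stronger readings are tempting but unsupported.
- *Allocation is unstratified.* Assessment of eligibility and randomization gives a 1/1/1 ratio and says allocation is made "using an automated computer-based random integer generator". It is silent on strata, and silence in an article does not settle the matter.
- *Precision is certainly lost.* That needs a sex difference in T2 units at equal T1 units, which the documents do not report.
- *Chance sex imbalance is a further harm.* Under simple randomisation the share of men would differ between two arms with an SD of about √(0.25 × 2/176) = 5 percentage points. This is not bias, and the standard error already reflects it. It is the same loss seen from another side.
- *The low-risk response and its number needed to treat suffer in the same way.* Response is a secondary binary outcome whose limits already differ by sex. The calculations here do not cover it.

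**Conclusion.** The point holds as a minor, optional improvement. The only covariate named for the primary model is the baseline score, although sex is known for everyone and may carry information that one noisy baseline week does not. The planned comparison is unbiased with a valid standard error, and 528 stands. The likely gain is 0% to about 9% of the residual variance, or 0 to about 3 points of power at d = 0.30 with 176 per arm. It is close to nothing if men's and women's usual drinking is equal. The size rests wholly on assumed distributions of usual drinking, week-to-week noise and the T1–T2 correlation. The mechanism is sound, but its strength in this trial is unknown.

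**What to change.** In Clinical evaluation, prespecify for weekly standard units: *ANCOVA with the baseline score and sex as covariates*. If an analysis plan exists, use the same wording there. The cost is one phrase and one degree of freedom; no new data are needed, and neither the sample size nor the contrasts change.

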However, all described interventions were tested in very specific populations, for example, military personnel [32], adolescents [31], individual companies [33], thus, it is questionable, if findings can be generalized to other workforce populations. Moreover, to the best of our knowledge, none of these studies included an economic evaluation. All of the interventions mentioned above are based on a self-help paradigm. However, unguided web-based interventions, that means those without any human support (i.e., pure self-help), have been found to be less effective than guided interventions for depression and social phobia [34]. With regard to interventions for problematic alcohol consumption, the picture is less clear. In a recent meta-analysis, Riper and her co-authors [28] did not find differences in terms of efficacy between guided and unguided interventions across different studies, but the number of trials with guidance was very small (*n* = 5). Thus, there is a need to explore the (cost-)effectiveness of web-based interventions for reducing problematic alcohol consumption with and without guidance in the same study.

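### Taken from one three-arm ANCOVA, each control contrast borrows variance from the arm it does not compare, so its standard error is mildly off if the arms differ in spread (minor, optional fix)

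*Protocol article*

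**What the plan says.** Under Clinical evaluation the protocol article sets the model: "Analyses of covariance with baseline scores as covariate will be conducted to explore the effects of the interventions compared to the control group". It adds: "A-priori contrasts will be defined to test the separate effects of the guided and unguided interventions compared to the control condition". The test level follows: "For all statistical analyses, significance level will be set at p < .05 for two-sided tests". Allocation is 1:1:1 (Assessment of eligibility and randomization).

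The primary outcome is alcohol standard units over the seven days before T2. Drinks are converted to units and "added to calculate the total sum score of units for the last 7 days" (Primary outcome), so the score cannot fall below zero.

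The two control contrasts are aims 1 and 2 of the study. The comparison of guided with unguided training is a secondary, exploratory aim.

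The article does not name the variance estimator for the contrasts. It mentions pooling only for the SD of change scores used in Cohen's d. It gives no arm-specific SD, coefficient of variation or SD ratio.

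**The concern.** An ordinary ANCOVA with three arms estimates one residual variance from everyone. A contrast of unguided training with control then rests partly on the scatter in the guided arm, although that arm is not in the comparison. If the three spreads are equal, this only adds degrees of freedom. If they differ, the standard error is wrong, and equal arm sizes do not cure it for a pairwise contrast among three arms.

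The spreads may differ here. Training that cuts drinking roughly in proportion to its level shrinks the SD along with the mean. Training that makes a minority abstinent and leaves the rest unchanged can widen it.

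The case where one format works and the other does not is a live one. The background notes that unguided programmes "have been found to be less effective than guided interventions for depression and social phobia", while calling the evidence on alcohol less clear. At stake is whether the p-values and intervals for the two main comparisons hold their nominal level.

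**Working it through.** **Inputs from the protocol article**
- Sample size: "We aim to include 528 participants", which is 528/3 = 176 per arm at 1:1:1.
- Design effect: "This sample size will allow us to detect an effect size of d = 0.30", at 80% power.
- Two-sided level 0.05.

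**Assumed, not in the document:** r = SD of an effective arm divided by the SD of an arm with no effect (control included).

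**Step 1. The plan's own figure.** A two-sample t-test with a common SD, d = 0.30 and 176 per arm has power 80.1%, and 3 x 176 = 528. The figure reproduces. The common SD belongs to that calculation and says nothing about the spread after treatment.

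**Step 2. One format works, the other does not.** Set the SD of control and of the ineffective arm to 1.
- Pooled variance = (2 + r²)/3.
- Ineffective arm against control: the correct average variance is 1, so used SE / correct SE = √((2 + r²)/3), and the two-sided error = 2[1 − Φ(1.96 × that ratio)].
- Effective arm against control: the correct average variance is (1 + r²)/2, so the SE ratio = √{[(2 + r²)/3] / [(1 + r²)/2]}.

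Example, r = 0.85: pooled variance = (2 + 0.7225)/3 = 0.9075, SE ratio = 0.953, error = 2[1 − Φ(1.867)] = 6.2%.

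| r | Ineffective arm: SE ratio | Two-sided error | False benefit (half) | Effective arm: SE ratio | Its 95% CI coverage |
|---|---|---|---|---|---|
| 0.75 | 0.924 | 7.0% | 3.5% | 1.046 | 96.0% |
| 0.85 | 0.953 | 6.2% | 3.1% | 1.027 | 95.6% |
| 0.90 | 0.968 | 5.8% | 2.9% | 1.017 | 95.4% |
| 1.00 | 1.000 | 5.0% | 2.5% | 1.000 | 95.0% |
| 1.20 | 1.071 | 3.6% | 1.8% | 0.969 | 94.3% |
| 1.30 | 1.109 | 3.0% | 1.5% | 0.956 | 93.9% |

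Solving for r, an error of 6% needs r = 0.87 and an error of 7% needs r = 0.75.

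**Step 3. What would produce such a ratio?** Under a proportional reduction, d = 0.30 lowers the mean by 0.30 × CV of itself, so r = 1 − 0.30 × CV. An assumed CV of 0.4, 0.6 or 0.8 gives r = 0.88, 0.82 or 0.76, and an error of 6.0%, 6.4% or 6.9%.

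**Step 4. Simulation.** Three-arm ANCOVA, skewed baseline and outcome, 176 per arm, 20,000 trials per scenario, d = 0.30 in one arm, assumed CV 0.4, 0.55 and 0.7. Two-sided rejection for the ineffective arm against control:

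| Form of the effect | Residual SD ratio | Pooled three-arm variance | Only the two arms compared |
|---|---|---|---|
| Additive shift | 1.00 | 4.9-5.2% | 4.9-5.2% |
| Proportional reduction | 0.88 / 0.84 / 0.79 | 5.7% / 6.2% / 6.8% | 4.8-5.1% |
| Minority with a large reduction | 1.15 / 1.05 / 0.97 | 4.1% / 4.7% / 5.0% | 4.7-5.0% |
| Minority becoming abstinent | 1.33 / 1.21 / 1.12 | 2.8% / 3.6% / 4.1% | 4.9-5.1% |

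Separate simulations of 4,000 trials per setting (Monte Carlo SE about 0.4 percentage points) applied HC3 to a proportional effect. They gave 4.6-5.2%, against 5.8-6.8% with the pooled SE. With no effect in either arm the rates were 4.4% (HC3) and 4.6% (pooled).

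**Step 5. Both formats work, as the plan expects.** Pooled variance = (1 + 2r²)/3. At r = 0.85 this is 0.815.
- Control contrasts: correct average variance (1 + 0.7225)/2 = 0.861, SE ratio √(0.815/0.861) = 0.973, coverage 94.3%.
- Guided against unguided: SE ratio √(0.815/0.7225) = 1.062, so that SE is 6% too large.

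**The case against.** The strongest reply is that the article never says the variance is pooled. It names ANCOVA and planned contrasts, and the choice of estimator is a detail that an analysis plan may settle. That stands. The point depends on the usual reading of the model and is not a demonstrated error in the text.

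A reader might infer that the ineffective format is bound to be declared effective in 6-7% of trials whenever only one format works. The document does not support this, for two reasons. A difference in means alone causes no inflation: with equal spreads the error is 5%, and with a wider spread in the effective arm it is below 5%. Also, 6-7% counts rejections in both directions, and false benefit is about half of that.

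The article also gives grounds to expect a mixed response. Participants may aim to cut down in certain situations, to abstain or only to monitor (Intervention), and some are expected to stop using the programme (Discussion). Such a mixture can widen the effective arm's spread. The plan expects both formats to beat control, and the alcohol meta-analysis it cites found no difference between guided and unguided formats, although few trials had guidance.

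This removes any claim to know the direction of the error. It does not remove the dependence on equal spreads: when the spread widens, the short standard error moves to the effective arm's own contrast.

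**Conclusion.** The point holds in a limited, conditional form. Read as one three-arm model with the default error term, the planned contrasts are mildly miscalibrated if the arms differ in spread, in a direction that cannot be known beforehand.

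Across the assumed SD ratios of 0.75 to 1.3, the two-sided error for an ineffective format runs from about 7% down to about 3%. Coverage for an effective one runs from about 96% down to about 94%. At a ratio of 1 there is no error.

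The SD ratio is an assumption throughout, and so is the pooled error term. Classical ANCOVA with planned contrasts remains a standard choice, and the sample size is unaffected. This is a minor robustness improvement.

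**What to change.** Under Clinical evaluation (or in the analysis plan, if it does not already say so), keep the ANCOVA and the planned contrasts. Add that standard errors will be heteroscedasticity-consistent (HC3) or based on arm-specific residual variances. Apply this to both control contrasts and to the exploratory comparison of guided with unguided training.

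The cost is one line of wording. It needs no new data and no change to the 528 participants. If variances turn out equal, the loss is negligible: the simulated error was 4.4% with HC3 against 4.6% with the pooled SE, a difference within Monte Carlo error.
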